#### Exclusion criteria

Patients will be excluded from the study in the following circumstances: under guardianship, medical contraindication to physical exercise, anti-arrhythmic or beta-blockers treatment and/or heart failure (left ventricular ejection fraction (LVEF) < 40% measured using echography pre or post-therapy). Patients who participate in another clinical study about non-pharmacological intervention will also be excluded to avoid potential bias in evaluation of quality of life enhancement.

### Interventions

#### APA program

The APA program will consist of supervised aerobic and resistance training at moderate intensity of 12–14 on the Borg scale, corresponding to 70–80% max heart rate [16]. It will be supervised by an APA instructor during 12 weeks with 1-h sessions twice a week. The intensity will be progressive, adapted to individual capacities and functional limitations of each patient. This intervention will be done in small groups to promote exchange and conviviality and to optimize the rates of participation and compliance. Each session will be composed of four sections: 5-min warm-up, 30-min aerobic training, 20-min resistance training, and 5-min cool-down. Warm-up will include soft joint movements to prevent injuries. Aerobic training could involve a walking protocol (Fig. 1) or step aerobic exercises. Resistance training will consist of circuit training with various muscular reinforcement exercises. Finally, there will be 5-min of stretching exercises for the cool-down.

**Fig. 1 Fig1:**
[figure not shown]
Walk protocol adapted from Mello [43]. White: rest; light grey: normal speed (7–9 Borg Scale); dark grey: accelerated speed (10–13 Borg Scale)

The walking protocol for weeks 1–6 will alternate between periods of walking at a comfortable speed and rest. Weeks 7–12 will include periods of walking at an accelerated speed and walking at a comfortable speed, as describe in Fig. 1. This 12-week protocol is adapted from and inspired by a treadmill program over 6 weeks previously tested in hematologic patients [44]. The walking protocol will take place on flat ground and stairs in the hospital park to promote functional rehabilitation in natural surroundings. In case of rain and to diversify the activity, step aerobics could be offered as an exercise in the fitness room of the hospital. The step aerobics will consist of choreographed movements to music. This activity requires cardiovascular adaptations and stimulates physical coordination, balance, and cognitive abilities such as memory or attention. In addition, it is a playful activity that promotes conviviality [45, 46].

Resistance training will be implemented to increase muscle strength and to reinforce stability, coordination and flexibility. Reinforcement of muscle chains, such as upper/lower limb (e.g., arm curl, squats) or lap belt (e.g., plank, modified curl-up) will be carried out with body weight, dumbbells (1–2 kg) or medicine balls (3–5 kg). These workouts will consist of a circuit training model including team challenges and games. We will closely survey all patients and pay particular attention to their form and posture to prevent pain and injuries. All of the exercises may be adapted according to each person’s abilities.

At the end of the APA program, patients will be encouraged to continue regular physical exercise at home, with friends or family, or with a club or association.

#### HRVB training

HRVB will include 10 supervised, 1-h sessions spread evenly over the course of the 12 weeks and will be supervised by the APA instructor in a dedicated room at the hospital. Sessions will consist of exercises using the Symbiofi® cardiac coherence software (SymbioCenter® technology, SymbioLine® Professional, SYMBIOFI, Loos, France) that provides various interactive workouts to control the rhythm and amplitude of respiration in order to achieve a cardiac coherence state with an elevated cardiac coherence score. To help patients achieve the cardiac coherence state, they will see their cardiac coherence score displayed on the screen along with a respiratory guide at 6 breaths/min and the feedback of HRV in real time (tachogram) from a plethysmograph pulse sensor.

The first two of the ten supervised sessions will provide exercises based on relaxation techniques to breathe consciously and focus on abdominal breathing. The following sessions will include interactive exercises with biofeedback reflecting cardiac coherence state. For example, a patient will see displayed on a screen a changing landscape from stormy to sunny weather according to the cardiac coherence score. The last HRVB sessions will include exercises that require more autonomy using only relaxing music and pictures. Each session will end with a 5-min HRV recording with respiratory guidance at 6 breaths/min to compare cardiac coherence scores from one session to the next.

At the first session, the following instruction will be given: *“You are going to participate in a 10-session program in which you will perform breathing exercises that will help alleviate your symptoms. You will have to come to the hospital center to do your training every week for 10 weeks. This intervention will be complementary to the adapted physical activity program that you will follow. I ask that you do not talk about what you do during these cardiac coherence trainings during your physical activity sessions, since some patients will not be doing this program.”**“We will be using a device with a pulse sensor to measure your heart rate. We will perform exercises that will allow you to control your breathing at a slower pace than usual. This breathing should produce strong, positive effects on your nervous and cardiovascular systems and help you to feel better.”**“The cardiac coherence training includes a part that should be done at home, with daily exercises. You should use the DODOW® device 20 minutes a day. This device is a light metronome to help you synchronize your breathing. A light is projected on the ceiling and you have to inhale when the light beam increases in brightness and to exhale when the light beam decreases in brightness. You will need to do this exercise each day at the same time, whenever you prefer. You can do this exercise just after waking up or before dinner, for instance.”*

Throughout the protocol, patients will have to practice cardiac coherence 20-min daily at home by controlling their breathing at 6 breaths/min, according to Lehrer’s protocol [47]. They will continue their home-based breathing exercises after completing the 10 supervised sessions and until the 12-week follow-up, when the study will be terminated. We will offer patients a light metronome (DODOW®, LIVLAB® technology, Paris, France) to assist in synchronizing their controlled breathing. The home-based practice will be registered in a logbook with date, duration and satisfaction, and will be monitored by the APA instructor.

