#### Physical condition assessment

Physical function will be evaluated with a 6-min walk test [59] and 50-ft walk test at fastest speed [60]. Muscular strength will be estimated from grip strength measured with a dynamometer for which values are correlated to general muscle mass [61]. The MCID of 6-min walk test is estimated at 25 m [62] but no MCID is known for 50-ft walk test and grip strength in chronic patients. Stability will be measured with a single limb stance test (eyes open and closed) and flexibility will be evaluated on both the lower and upper body. All of these assessments have been previously tested in hematologic patients or in the elderly; they are adapted and feasible for our study population [63–65].

The APA instructor will administrate the Global Physical Activity Questionnaire (GPAQ) to evaluate daily activities. The French version of GPAQ is validated by the World Health Organization [66] and collects information about three domains of physical activities (activity at work, travel to and from places, and recreational activity) and sedentary behavior.

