**Fig. 2 Fig2:**
[figure not shown]
Timeline of the APACCHE study

At T0, hematologists will deliver a brochure about the APA program and a briefing note regarding the protocol to potential participants. They will complete a dedicated form related to the medical prescription of the APA program including details about clinical status and specific recommendations for the APA instructor. Then, the APA instructor will contact interested patients to make a first appointment (T1).

At T1, the hematologist will obtain informed consent from the patients, and will proceed to the randomization. For study participants who will be included in the experimental group, a clear description about HRVB training will be given by the APA instructor.

At T1, T2, T3 and T4, quality of life, fatigue, anxiety and depression will be assessed by trained interviewers. Clinical status will be collected by the hematologist and HRV level, cardiac coherence score, and GPAQ will be measured by the APA instructor. Physical tests will be conducted only at T1, T2 and T3. (Table 1).

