#### Blinding and intervention assignment

The specificity of the HRVB and APA interventions will not allow for the use of double-blind assignments for the APA instructor and hematologists. However, we will establish a blinding on the questionnaire assessments for the trained interviewers to maintain a high level of evidence.

Randomization will be balanced in both groups, with a 1:1 allocation ratio, without stratification. The randomization list will be established by the statistician from the Methodology and Data Management Centre before the start of the research. Different sizes of randomization blocks will be used to leave the investigators blind to their size and to avoid predictable allocation. Randomized block sizes of 4,6,8 or 10 blocks will be performed on STATA®. The randomization list will then be imported into the CsRandom module of the Ennov Clinical® electronic case report form (eCRF), which the investigator will use to perform the randomization.

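### Interviewer blinding is the only blinding of people stated, yet patients are asked for silence only in exercise sessions, and the GPAQ falls outside the blinding

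*Protocol article*

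**What the plan says.** Under Blinding and intervention assignment, the protocol article says that the nature of the interventions "will not allow for the use of double-blind assignments for the APA instructor and hematologists". It then states its one safeguard on outcome assessment: "we will establish a blinding on the questionnaire assessments for the trained interviewers to maintain a high level of evidence". Varying and concealing the block sizes, described in the same section, protects allocation and is not outcome blinding.

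Under Evaluation times and implementation, at T1 to T4, "quality of life, fatigue, anxiety and depression will be assessed by trained interviewers". The same paragraph says that "HRV level, cardiac coherence score, and GPAQ will be measured by the APA instructor". Physical condition assessment agrees: "The APA instructor will administrate the Global Physical Activity Questionnaire (GPAQ) to evaluate daily activities". The HRVB training section adds that the HRVB sessions "will be supervised by the APA instructor in a dedicated room at the hospital", and the APA program section has an APA instructor supervise the exercise sessions too. The person who gives the GPAQ therefore knows the allocation.

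The HRVB training section prints the instruction read to HRVB patients at their first session. The part on disclosure is "I ask that you do not talk about what you do during these cardiac coherence trainings during your physical activity sessions", and the reason given is "since some patients will not be doing this program".

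Database and data monitoring gives the interviewers limited database rights and names blinding as the reason.

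**The concern.** The outcomes that carry the trial, above all the QLQ-C30, are patient reports collected by interviewers. The article ties its claimed level of evidence to those interviewers not knowing the arm. The patient is the most obvious person to reveal it. HRVB patients know their group, practise breathing every day until the follow-up visit, and are then asked about fatigue, mood and quality of life. The authors foresaw that patients would talk and wrote a rule, but the rule names only the exercise sessions. A patient who follows it exactly is free to mention the breathing training to an interviewer. An interviewer who learns the arm could, without meaning to, prompt or record answers differently.

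The GPAQ raises a related but separate point. It is a self-report questionnaire, yet patients answer it to the person who trains them. Scheduled contact with that person is greater in the HRVB arm, so any wish to please the trainer could differ between arms. Statistical analysis plans t-tests on the sub-scores of each questionnaire, which on its wording takes in the GPAQ.

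**Working it through.** No figure in the article depends on this point, and the planned 70 patients are not affected. The check sets the sections side by side and counts exposure.

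**1. What supports the interviewers' blinding**

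| Route by which an interviewer could learn the arm | Safeguard shown |
|---|---|
| Reading it in the eCRF | Limited access (Database and data monitoring) |
| Being told by the patient | None; the script covers exercise sessions only (HRVB training) |

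The reason attached to the script concerns fellow patients who are not doing HRVB. It does not mention interviewers, and no other section shown asks patients of either arm to withhold their group at assessments.

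**2. How many interviews are exposed**

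- Interview visits after baseline: T2, T3 and T4, so 3 per patient.
- HRVB arm, 35 patients planned (Sample size): 35 × 3 = 105 interviews.
- Both arms, 70 patients, since a control can also reveal the group: 70 × 3 = 210 interviews.

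These are scheduled interviews before any dropout. They count opportunities and do not estimate how often disclosure happens.

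**3. Which questionnaires lie inside the blinding**

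| Questionnaire | Given by | Blinded assessor |
|---|---|---|
| QLQ-C30, SF-36 | Trained interviewers | Yes, as planned |
| MFI-20 | Trained interviewers | Yes, as planned |
| HADS | Trained interviewers | Yes, as planned |
| GPAQ | APA instructor | No |

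The two sections that assign the GPAQ agree with each other, so there is no contradiction about who gives it. The blinding statement speaks of questionnaire assessments without excepting the GPAQ, so a reader could wrongly take it to be covered.

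**4. Scheduled contact with the instructor before the T3 GPAQ**

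- APA, both arms: 12 weeks × 2 sessions × 1 h = 24 h.
- HRVB, experimental arm only: 10 sessions × 1 h = 10 h.
- Experimental arm total: 24 + 10 = 34 h.
- Ratio: 34 / 24 = 1.42, or 42% more.

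This assumes full attendance. It shows that contact differs between arms; it does not measure bias.

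**The case against.** The strongest reply is that this is an omission from a condensed article. The script is the opening instruction of the HRVB programme, written to limit contamination between patients. It does not claim to set out how interviewers are kept blind, and reminders at assessment visits may well stand in the full protocol. This has force, and it rules out saying that the trial has no such procedure. It does not dispose of the point, because the instruction is printed as the text to be given, it deals with disclosure, and it names a single setting. The proposal improves a sentence the authors chose to fix.

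A reader might go further and infer that questionnaire blinding is not delivered. The document does not support that, for three reasons:

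- The promise is limited to the trained interviewers, and the GPAQ was never among their assessments. Giving it to the instructor unblinds no interviewer.
- The restricted eCRF access shows that blinding was put into practice in at least one respect.
- An unprotected route does not show that anyone takes it.

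Other tempting additions also fail. The article does not say that the interviews are face to face. It says that patients will be encouraged to keep exercising after the programme, but it does not say that the instructor does this, and the encouragement is not confined to one arm.

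Two further objections stand in part. The GPAQ is not named among the abstract's primary or secondary outcomes or in the hypotheses, so no headline claim rests on it. Moving it to the interviewers could also prompt talk of daily activities, including breathing practice; asking it last answers that within a visit.

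Finally, patients know their arm, and HRVB patients are told to expect benefit. Perfect interviewer blinding would leave that expectation bias in place.

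**Conclusion.** The point holds in a limited form. Interviewer blinding is the only blinding of people that the article states, and restricted database access is the only support shown for it. Disclosure by the patient at T2, T3 and T4 is left unprotected. The GPAQ lies outside the blinding because the unblinded instructor who delivers both interventions gives it; this does not touch the QLQ-C30, SF-36, MFI-20 or HADS interviews.

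The exposure is three interviews per patient, and 42% more scheduled instructor contact in the HRVB arm before the T3 GPAQ. The resulting bias, in points or in direction, cannot be derived from the document. The conclusion assumes that no further instruction to patients exists in the full protocol; if one does, the first part reduces to a request to mention it. The trial is not invalidated, but its stated evidential safeguard lacks a simple support, and adding it is worthwhile.

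**What to change.** 1. In the HRVB training script, extend the request for silence so that it also covers the people who give the questionnaires. Give control patients an equivalent request about their own programme.
2. Have each interviewer open the T2, T3 and T4 interviews by reminding the patient not to mention the group or its activities.
3. Have the blinded interviewers, already scheduled at T1 to T4, give the GPAQ after all the other questionnaires, so that any disclosure it prompts cannot affect that visit's other answers. Change Physical condition assessment and Evaluation times and implementation to match. If the instructor must keep it, state under Blinding and intervention assignment that the GPAQ is unblinded.
4. Optionally, record each interviewer's guess of the arm at T3, so that the blinding can be described in the report.

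The cost is a sentence in the script for each arm, a short reminder and a few more minutes of interviewer time, plus one eCRF item if the guess is recorded. The sample size and the planned analyses do not change. The report should still acknowledge that patients knew their arm, since none of these steps removes expectation bias.

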#### Statistical analysis

To evaluate effectiveness of HRVB, we will compare the average evolutions (T3-T1 difference score) between the experimental group (HRVB+APA) and the control group (APA). Student’s t-test will be performed for the different dimensions and scale sub-scores of each questionnaire, as well as cardiac coherence score and SDNN. An analysis of longitudinal data collected at T1, T2, T3 and T4 will be conducted using a linear mixed model with structured covariance residuals. The bivariate survival analysis (death and / or relapse, survival without serious infectious events) will be carried out using the Kaplan-Meier method. Group comparison will be calculated using the log-rank test.

All hypotheses will be tested in a single analysis, intention to treat (according to the group assigned by the randomization), bilaterally at the threshold α = 5%. The analyses will be performed with SAS® (version 9.4, SAS Institute Inc., Cary, NC, USA). At the end of the research study, investigators will anonymize the collected data and results will be submitted to the research partners. The statistician, methodologist and investigators will have access to the final dataset. An article in a journal indexed on Medline will be carried out in post-trial.

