## Discussion

Previous studies have investigated the effectiveness of HRVB compared to physical exercise [67–69]. To the best of our knowledge, there have been no studies about the added value of HRVB on physical exercise to enhance overall quality of life. While recent studies about HRVB training have demonstrated the feasibility and the effectiveness of HRVB in chronic patients [37, 41, 42], it has not yet been done in cancer patients, namely in hematology. Most clinical studies conclude that HRVB can reduce symptomatology of chronic disease and improve HRV level, supporting our hypothesis that HRVB may be feasible and effective in recovery of hematologic patients.

We hypothesize that HRVB associated with an APA program will be more effective than an APA-only program in improving quality of life during post-treatment in adult hematologic patients and expect the following outcomes from this experimental group: i) significant improvements in overall quality of life and a reported decrease in overall fatigue, anxiety and depression; ii) increased HRV levels, reflecting a better physiological regulation through autonomic control of the heart; iii) better BMI and BP measurements; and iv) less infectious events, relapses and deaths. All of these variables should be improved between T1 and T3. The results recorded at T3 could be sustained through T4, especially if patients are persistent with their home-based practice for both cardiac coherence and physical exercise.

All participating patients will be in remission for hematologic malignancies that have required hospitalization, caused sudden disruptions to their day-to-day lives, and/or have required particular aggressive treatments with high-dose chemotherapy, affecting patients’ overall quality of life. To avoid age-related effects, we have chosen a within-subject design and will exclude patients over 70 years.

Our short-term HRV recording protocol is based on the recommendations from Task Force [70] and more recently from Laborde [57], who has suggested guidelines for psychophysiological research. Although electrocardiogram is more accurate, we use the pulse sensor to assess pulse-to-pulse interval data which accurately approximates the inter-beat interval [71]. To analyze HRV data in time-domain and frequency domain, *HRVanalysis* will be used [58].

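### The fixed HRVB script promises symptom relief that the trial is meant to test, and its request for silence does not cover the questionnaire interviews

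*Protocol article*

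**What the plan says.** Under HRVB training, the protocol article sets out word for word what patients hear at their first biofeedback session. Only the HRVB+APA arm attends it. Patients are told that "you will perform breathing exercises that will help alleviate your symptoms" and, later, "This breathing should produce strong, positive effects on your nervous and cardiovascular systems and help you to feel better". They are also asked for discretion: "I ask that you do not talk about what you do during these cardiac coherence trainings during your physical activity sessions". The reason given is that some patients are not in the HRVB programme.

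On outcome assessment, Evaluation times and implementation states that at T1 to T4 "quality of life, fatigue, anxiety and depression will be assessed by trained interviewers". Blinding and intervention assignment concedes that the instructor and hematologists cannot be blinded, and adds: "we will establish a blinding on the questionnaire assessments for the trained interviewers to maintain a high level of evidence". Database and data monitoring restricts what the interviewers can see in the database, for the sake of that blinding.

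The Statistical analysis section opens: "To evaluate effectiveness of HRVB, we will compare the average evolutions". It defines these as T3 minus T1 differences, compared between arms with Student's t-test.

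On existing evidence, the Discussion says "there have been no studies about the added value of HRVB on physical exercise to enhance overall quality of life", and of HRVB itself that "it has not yet been done in cancer patients, namely in hematology". The same section, and the Background on HRVB, also cite favourable results in other chronic diseases.

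**The concern.** The script tells one arm, as settled fact in one phrase and as a confident expectation in another, that symptoms will ease and that they will feel better. For this population and this add-on comparison, that is the question the trial is run to answer. Patients then rate their own quality of life knowing which programme they had.

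A promise of benefit can act in two ways. It may make patients feel better; in an add-on trial that belongs to the effect of the programme. Or it may lead them to answer more favourably without feeling better; that is response bias. The planned data cannot separate the two. Only the second is a fault, and the promises invite it without need.

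Blinding the interviewers limits their influence on the answers. It does nothing about the respondent's own expectations. It also works only while interviewers remain unaware of the arm, and the one scripted request for discretion is not aimed at them.

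**Working it through.** **Do patients know their arm?** The protocol does not say so outright, but it follows. HRVB is described to experimental patients after randomization (Evaluation times and implementation), and the script tells them that others are not doing it.

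**Does the script fall inside the primary contrast?** Consent and randomization take place at T1, and HRVB sessions run during the 12 weeks that follow. Anything the script adds to later answers therefore stays in the T3 minus T1 difference. What matters is the excess over any similar effect in the APA arm, and the instructions to that arm are not shown.

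**What does the evidence in the protocol support?** It reports benefit of HRVB in other chronic diseases, and effects on the cardiorespiratory and autonomic systems. It reports no study in cancer patients and none of HRVB added to exercise. A hypothesis is supported; a promise of symptom relief to these patients is an extrapolation.

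**What protects the interviewer blind?** The request for silence names physical activity sessions only. Restricted database access stops interviewers from reading the arm, but not from hearing it. With 35 HRVB patients and interviews at T2, T3 and T4, up to 35 × 3 = 105 interviews, 35 of them at T3, fall outside the scripted request.

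**Sample size, reproduced first.** Inputs from Sample size: difference 5, SD 7, two-sided alpha 5%, power 80%, 10% missing or dropout.
- n per arm = 2 × 7² × (1.960 + 0.842)² / 5² = 30.8, rounded up to 31.
- 31 / 0.9 = 34.4, rounded up to 35 per arm, or 70 in total. This agrees with the plan and is not in dispute.

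**Sensitivity to an assumed reporting shift.** Evaluable patients: 70 × 0.9 = 63, split 32 + 31, so 61 degrees of freedom and critical t = 2.00.
- SD 7: SE = 7 × √(1/32 + 1/31) = 1.764; critical difference 2.00 × 1.764 = 3.53.
- SD 14 (an assumption, twice the protocol's value): SE = 3.528; critical difference 7.05.

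With no true effect and a between-arm shift b favouring HRVB, the noncentral t distribution with noncentrality b/SE gives the chance of a significant result favouring HRVB:

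| b (points) | SD 7 | SD 14 |
|---|---|---|
| 0 | 2.5% | 2.5% |
| 0.5 | 4.6% | 3.4% |
| 1 | 8.0% | 4.6% |
| 2 | 19.9% | 8.0% |
| 3 | 38.7% | 13.1% |

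The chance reaches 5% at b = 0.565 for SD 7 (0.565/7 = 0.08 SD; 0.565/5 = 11% of the effect sought) and at b = 1.129 for SD 14. Every b here is an assumption. The table would look the same for any unblinded trial of this size with a patient-reported outcome.

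**The case against.** Several counter-arguments have force.

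- **The promise is not groundless.** A reader might infer that the Discussion contradicts the script. It does not. The sentence that notes the absence of cancer studies begins by citing effectiveness in chronic patients, and the Background supports effects on the cardiorespiratory system and well-being. The script also never claims that HRVB plus APA beats APA. This stands: the fault is extrapolation stated as a promise.
- **The control arm may be encouraged too.** APA is prescribed by a hematologist and introduced with a brochure, for everyone. Only a difference in expectation biases the comparison, so similar encouragement for APA would shrink the net effect. This stands, and it is one reason why the size cannot be given.
- **Silence about interviewers is not proof of a gap.** The scripted request serves to limit contamination between patients. A separate instruction not to reveal the arm could sit in the full protocol or the consent material. This stands too. What can be said is that the script does not protect the blind and that the article describes only the database restriction.
- **A rationale is part of a behavioural treatment.** Patients must practise for 20 minutes daily, and an instructor who voices doubt could weaken the programme. This is a fair reason to avoid discouraging language. It is no reason to keep a promise of outcome.
- **Patients cannot be blinded here.** Agreed, and nothing in this point asks for it. Nor is the extra contact time in the HRVB arm at issue, since that is the declared add-on design.

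**Conclusion.** The point holds as a cheap improvement. Wording fixed in the protocol, heard by one arm only, promises the benefit under test to patients whose own answers form the primary outcome. That invites avoidable differential response bias in the T3 minus T1 contrast. The same script leaves the questionnaire interviews out of its request for discretion, although interviewer blinding is the protection that the protocol offers for these outcomes.

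The size is unknown. It rests on how far the wording changes answers rather than feelings, and on what APA-only patients are told; the documents show neither. A reader might take the 8% to 39% in the table (shifts of 1 to 3 points, SD 7) as the false-positive rate that the script causes. The documents do not support that: the shifts are assumed, and the script would account for an unknown part of any shift. The figures show only that, at this sample size, a shift well below the 5 points sought would matter. It would also go too far to say that the interviewer blind is unprotected, given the database restriction and possible instructions elsewhere. No stated sample size or analysis is wrong.

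**What to change.** 1. In the script, replace the phrase that promises symptom relief with neutral, non-discouraging wording, for example *breathing exercises whose effects we are studying*. Delete the sentence that promises strong effects and feeling better. Keep the technique and home-practice instructions as they are.
2. Add a request, given to both arms because an APA-only patient can also reveal the allocation: *Please do not tell the person who asks you the questionnaires which programme you follow.* If the full protocol already contains such a request, only a cross-reference is needed.

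The cost is a written amendment validated by the ethical committee, as Design and setting requires. No patients, visits or instructor hours are added, and the sample size is unchanged. The possible downside is slightly less enthusiasm for daily home practice; the planned logbook would show this, though it would not repair it.
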